#### **12.2.3. Adverse Event Follow-up**

Patients with non-serious adverse events that are ongoing at the patient's last study visit must be followed until resolution or for 30 days after the patient's last study visit, whichever comes first. Non-serious adverse events that are reported during the 7 days following the patient's last study visit will be recorded on the Adverse Events electronic CRF and followed until resolution or for up to the 30 days after the patient's last study visit, whichever comes first. Serious adverse events will be followed until the event resolves or the event or sequelae stabilize. Serious adverse events that are reported within 30 days of the patient's last study visit should be reported as indicated in [Section 12.5](#).

#### **12.2.4. Adverse Event Reporting Period**

Adverse events are to be recorded in the source documents from the time of the patient's informed consent signature until the end of the patient's study participation. Each adverse event, both serious and non-serious, will also be reported on the Adverse Events electronic CRF. CRF Completion Instructions will be provided to each investigational site. If the patient reports or the Investigator learns of a new AE(s) up to 7 days after the patient's last study visit or a new SAE(s) up to 30 days after the patient's last study visit, the investigational site personnel will ensure that these data are recorded on the Adverse Events electronic CRF for the study. The period during which an SAE must be reported may be extended if there is a strong suspicion that the event being reported is related to the study medication or a study procedure.

#### **12.2.5. Pre-existing Condition**

A preexisting condition is one that is present at the start of the study. A preexisting condition should be recorded as an adverse event if the frequency, intensity, or the characteristics of the condition worsen during the study period.

### **12.3. Relationship to Study Drug**

Each AE is to be reported on the AE electronic CRF. The Investigator is responsible for making an assessment of the likelihood that an AE is causally related to the study medication. The Investigator should choose one of the five choices of causality.

- **Certain:** occurs in a reasonable time after study drug administration and cannot be explained by concurrent disease or drugs. The event should

respond to withdrawal of study drug (de-challenge) and recur with re-challenge when clinically plausible.

- **Probable:** occurs in a reasonable time after study drug administration and it is unlikely to be attributed to concurrent disease or drugs, and it has a response to de-challenge. Re-challenge information is not required to fulfill this definition.
- **Possible:** occurs in a reasonable time after study drug administration, but could be related to concurrent disease or drugs. De-challenge information may be lacking or unclear.
- **Unrelated:** the event has an improbable temporal relationship (too soon, or too late after study drug, or study drug is not taken) and is plausibly related to other drugs or underlying disease.
- **Unassessable:** available information is insufficient, contradictory, and cannot be supplemented or verified at the time of the report. **This assessment will be considered as “related” for all expedited reports until an alternative assessment is made.**

## 12.4. Recording Adverse Events

### 12.4.1. Adverse Events during Study Period

At each study visit, the Investigator must seek information on adverse events by questioning the patient and, as appropriate, by examining the patient. Information on all adverse events should be recorded immediately in the source document, and also in the appropriate adverse event module of the electronic CRF. All signs, symptoms, and abnormal diagnostic procedure results that are considered clearly related should be grouped and recorded in the source document as one diagnosis. All adverse events occurring during the study period must be recorded.

### 12.4.2. Post-study Adverse Event

At the last scheduled visit, the Investigator should instruct each patient to report any subsequent event(s) that the patient or the patient’s personal physician believes might reasonably be related to participation in this study. The Investigator should notify the study sponsor of any death or adverse event occurring at any time after a patient has discontinued or terminated study participation that may reasonably be related to this study. The Investigator should also notify the sponsor if they become aware of the development of cancer or a congenital anomaly in any offspring conceived subsequent to a patient’s study participation.

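### The only patient instruction on post-study events (Section 12.4.2) asks for those believed study-related, so spontaneous reports in the causality-free 7-day AE and 30-day SAE windows can be selected by perceived cause

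*Protocol*

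**What the plan says.** Section 12.2.4 sets the recording rule after the last visit. It opens with a condition, "If the patient reports or the Investigator learns of a new AE(s) up to 7 days after" the last study visit, and adds "a new SAE(s) up to 30 days after" that visit. Once that condition is met, "investigational site personnel will ensure that these data are recorded on the Adverse Events electronic CRF for the study". Section 12.2.3 matches it: "Non-serious adverse events that are reported during the 7 days following" the last visit are recorded and followed, and SAEs reported within 30 days go through Section 12.5. Neither section attaches a relatedness condition to these windows. Section 12.2.4 brings in suspected relatedness only as a ground for extending the SAE period.

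Section 12.4.2 tells the investigator what to say to patients when they attend for the last time on schedule: they should report later events that they themselves or their "personal physician believes might reasonably be related to participation in this study". It gives no time limit and refers to neither window. A separate sentence there has the investigator tell the sponsor about deaths and adverse events "occurring at any time after a patient has discontinued or terminated study participation that may reasonably be related to this study".

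Under Section 12.4.1, patients are actively questioned about adverse events at study visits. The last scheduled visit ends on the morning of Day 37 (Section 10.2.2), and Table 2 shows no later contact. The early termination list in Section 10.2.3 includes an adverse event query but no instruction about later events.

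**The concern.** The windows are defined without regard to cause, in line with the AE definition in Section 12.2.1, which also does not depend on relatedness. For a new event after the last visit, however, what reaches the site depends largely on what patients think they have been asked to mention. If the request is framed around relatedness, events that look unrelated are less likely to be volunteered. Part of the causality judgement is then made before the event reaches the investigator, whom Section 12.3 makes responsible for it.

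At stake is how complete late SAE reporting and the AE listings are, in a trial that has withdrawal after abrupt cessation among its secondary objectives (Section 5.1.2). A sparse listing for the 7-day or 30-day window could be read as few events when it partly reflects how the request was worded. No efficacy endpoint is involved.

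**Working it through.** No figure in the plan needs reproducing. The check is a comparison of the provisions, followed by a day count on the nominal schedule.

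**Provisions side by side**

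| Provision | Time span | Relatedness condition | What triggers it |
|---|---|---|---|
| 12.4.1, questioning by the investigator | Study visits, the last ending Day 37 | None | Active query |
| 12.2.3 and 12.2.4, new AEs | 7 days after last visit | None | Patient reports, or investigator learns |
| 12.2.3 and 12.2.4, new SAEs | 30 days after last visit | None within the 30 days | Patient reports, or investigator learns |
| 12.4.2, instruction to patients | Open-ended | Belief of patient or personal physician | Patient decides to report |
| 12.4.2, investigator's notification | Open-ended | May reasonably be related | Investigator becomes aware |

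Rows two and three are passive: they come into play only when information arrives. Row four is the only place where the protocol prompts the patient to supply it, and it is the patient-facing row that carries a relatedness condition.

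**Day count, nominal schedule** (the visit window of ± 2 days would shift these days)

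- Last visit ends: Day 37.
- AE window closes: 37 + 7 = Day 44.
- SAE window closes: 37 + 30 = Day 67.
- Table cut-off under Section 14.10.1, 3 days after the final dose: 36 + 3 = Day 39 if the Night 36 placebo counts as the final dose, or 35 + 3 = Day 38 if the last double-blind dose on Night 35 does.
- Days after the last visit that can still reach the AE tables: 39 − 37 = 2, or 38 − 37 = 1.

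So 1 to 2 days of the 7-day window can enter the summary tables. The other 5 to 6 days lead to listings only, unless the event caused discontinuation.

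**What the instruction does not touch**

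- Events on Night 36 and Day 37 are queried directly. Day 37 also has a physical examination, ECG, laboratory tests, vital signs and the BWSQ (Section 10.2.2).
- Non-serious AEs ongoing at the last visit are followed to resolution or 30 days, whichever comes first, whatever the cause (Section 12.2.3).
- Patients who discontinue because of an AE or an abnormal laboratory or test result are followed until resolution or for 30 days, whichever is less (Section 7.3).

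What remains exposed is new-onset events after the last visit: up to Day 44 for AEs and Day 67 for SAEs.

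**The case against.** The strongest reply is that nothing here is contradictory. The windows cover events that are reported or learned of, so the protocol never promises to gather every event in them, and Section 12.4.2 breaches no such promise. It does not tell patients to report related events only; it asks for those and is silent on the rest. It can be read as an open-ended provision added to the windows. The judgement is also not left to the patient alone, since the personal physician's belief suffices, and the test is relation to taking part in the study, which is wider than relation to the drug. All of this stands. It limits the point to a risk of selective reporting.

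A reader might also infer that an unrelated death or hospitalisation 20 days after the last visit would escape the investigator's duty, because the notification sentence in 12.4.2 is tied to relatedness. The documents do not support that. Section 12.2.4 requires an SAE learned of within 30 days to be recorded, Section 12.2.3 sends it to Section 12.5, and Section 12.5.1 requires all serious events to be reported within 24 hours with no relatedness test. The open-ended sentence takes nothing away from those duties.

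A third inference would be that nearly all safety observation off the drug is filtered, or that withdrawal complaints in particular are lost. The unfiltered Night 36 and Day 37 assessments and the follow-up of ongoing events argue against the first. As to the second, symptoms just after stopping a sleep medication are among those a patient would most readily link to the study.

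Finally, consent pages are not in the text reviewed, and the Study Manual and CRF Completion Instructions are not shown. Patients may be told more elsewhere. What can be said is that this protocol contains no other such instruction.

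**Conclusion.** The mismatch is real and minor. The patient instruction in Section 12.4.2 is narrower than the windows it has to feed, and with no scheduled contact after Day 37 or early termination there is no planned query to correct for that. Spontaneous reports of new-onset events can therefore be selected by perceived relatedness. The effect falls mainly on late SAE reports and on listings; the AE summary tables are little affected.

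The size of any under-reporting cannot be estimated from the protocol. The conclusion assumes that investigators give the instruction as written, that patients act on it, and that no other patient material widens it. The stronger reading, that Section 12.4.2 overrides the 7-day and 30-day rules or restricts patients to related events, goes beyond the text.

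**What to change.** Reword the patient instruction in Section 12.4.2 so that patients are asked to report any new or worsening event for 7 days after the last visit and any serious event for 30 days, whether or not they or their physician think it related. Keep the reasonably-related wording for events after those periods. Give the same instruction at early termination and add it to the list in Section 10.2.3, since 12.4.2 now refers only to the last scheduled visit. State in one sentence that the open-ended investigator notification adds to the duties in 12.2.3, 12.2.4 and 12.5 and does not replace them.

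This needs no added visit or call. The cost is a wording change and a few more unrelated events to record. It should be made before enrolment, because events never volunteered are hard to recover later.

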### 12.4.3. Abnormal Laboratory Values

Abnormal laboratory values or test results should not generally be considered adverse events, unless deemed clinically significant by the investigator. Assessment of signs or symptoms or requirement for therapeutic intervention should be considered when

determining clinical significance. Record clinical significant laboratory values on the Adverse Events Case Report Form using an appropriate diagnostic description.

## **12.5. Reporting Adverse Events**

### **12.5.1. Study Sponsor Notification by Investigator**

All serious AEs should be reported by fax within 24 hours to the Vanda Drug Safety designee (Covance Drug Safety Services) using the Serious Adverse Event Report form. The Investigator will keep a copy of the SAE Report form on file at the study site. The SAE form and detailed instructions are provided in the Study Manual.

The initial report should contain as much information about the event as possible. Follow-up reports will provide any information missing at the time of the initial report (e.g., an end date for the adverse event or laboratory values received after the report). In addition, significant new information on ongoing SAEs should be provided promptly to Covance Drug Safety Services.

The initial and follow-up reports should identify patients by a unique patient ID rather than by patients' names, personal identification numbers, and/or address.

At the time of the initial report, the following information listed in [Table 5](#) should be provided at a minimum.

**Table 5: SAE Reporting Information**

|                                                                                                                                                                                                                                      |                                                                                                                                                                                                                                                                                                                |
|--------------------------------------------------------------------------------------------------------------------------------------------------------------------------------------------------------------------------------------|----------------------------------------------------------------------------------------------------------------------------------------------------------------------------------------------------------------------------------------------------------------------------------------------------------------|
| 

• Protocol Number

• Site Number

• Patient ID number

• Patient Initials

• A description of the event

• Date of onset

• Current status

 | 

• Intensity level of SAE

• Action taken regarding study medication administration

• The reason the event is classified as serious

• Investigator assessment of study medication relationship and SAE

• If the blind was broken

 |
|--------------------------------------------------------------------------------------------------------------------------------------------------------------------------------------------------------------------------------------|----------------------------------------------------------------------------------------------------------------------------------------------------------------------------------------------------------------------------------------------------------------------------------------------------------------|

### **12.5.2. EC/IRB Notification by Investigator**

Reports of all SAEs (including follow-up information) must be submitted by the Investigator to the EC/IRB within 10 working days. Copies of each report and documentation of EC/IRB notification and receipt will be kept in the Clinical Investigator's Study File.

## **12.6. Unblinding Procedures**

The patients and the medical staff will not be aware of which treatment is being administered. Data will remain blinded until clinical data have been reviewed, at which time the randomization schedule may be released for the purposes of assessment of drug safety.

Only if a patient's medical condition warrants, such as a medical emergency for which treatment requires knowledge of what study medication was given, may the Investigator break the blind to determine if the patient received active drug or placebo. In most instances of medical emergency, prior approval to break the code must be granted by the Medical Monitor. However, the code can be broken on the Investigator's request (by telephoning the IVRS) in those cases where the patient's condition is so severe that time would not permit prior approval. In any case, the study monitor must be informed as soon as possible by telephone following the event and by letter or e-mail explaining the details of the case with accompanying diagnostic reports, where appropriate. The Investigator must ensure that any communication with the Medical Monitor is blinded even after the Investigator has broken the blind.

### **13. PHARMACOGENOMIC ASSESSMENT**

Patients will be offered the option of participating in an additional study to identify genetic factors that may predict response to treatment with VEC-162 and/or relative susceptibility to side effects. Participating patients must provide a separate written informed consent to permit the collection of a blood sample for pharmacogenomic analysis. The pharmacogenomic protocol is described in [Appendix 21.3](#). While this exploratory assessment is optional to the patient, it should be noted that *PER3* genotyping is mandatory. Once this genotyping is finalized, any remaining sample will be destroyed by the sponsor and/or the sponsor's representative.

## **14. STATISTICS**

### **14.1. Statistical Methods**

This section describes the planned statistical analyses in general terms. A complete description of the methodology will be specified in a statistical analysis plan (SAP), which will be finalized prior to database lock. Any changes in the statistical methods described in this protocol that occur prior to database lock will be documented in the statistical analysis plan and will not require a protocol amendment.

#### **14.1.1. General**

The primary efficacy variable is the average Latency to Persistent Sleep (LPS) computed via PSG assessments from nights 1 and 8. The primary null hypothesis to be tested is that there are no differences among the treatments.

Statistical analyses will be performed using two-sided test. A 0.05 significance level will be used in all tests of treatment differences. Test for interaction will utilize a 0.10 statistical significance level.

For the primary efficacy endpoint, the type I error will be controlled via Fisher's protected least significant difference (LSD). Using this procedure, an overall test of the treatment effect will be conducted and pairwise comparisons will be examined only if the overall treatment is significant at the 0.05 alpha level. Pairwise comparisons will also be examined at the 0.05 significance level.

In addition, for labeling purposes only, the experiment wise Type I error will be controlled to a maximum of 5%. A gatekeeper strategy will be employed such that any secondary endpoints will be considered for statistical significance only if the primary endpoint to be statistically significant.

Data will be summarized by treatment group (and by visit when applicable), with respect to demographic and baseline characteristics, efficacy variables, and safety variables.

Summary statistics will include the mean, N, standard deviation, median, minimum, and maximum values for continuous variables, and frequencies and percentages for categorical variables.

Continuous variables such as latency to persistent sleep (LPS), wake after sleep onset (WASO), total sleep time (TST) and sleep efficiency (SE) will be analyzed using an ANCOVA model with treatment and pooled center as main effects, baseline as a covariate and the treatment-by-baseline interaction. An exploratory analysis will be performed to explore whether there are treatment-by-center interactions. If a treatment-by-center interaction is detected, the interaction will be explored in an ad-hoc manner.

Categorical variables will be analyzed using Cochran-Mantel-Haenszel (CMH) test blocking on centers (or pooled centers).

Details of the model and the analyses will be specified in the SAP. All statistical analyses will be performed using SAS®, Version 8.2 or higher.

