## **5. TRIAL OBJECTIVES AND RATIONALE**

### **5.1. Objectives**

#### **5.1.1. Primary Objective**

1. To assess the effects of 20 and 50 mg VEC-162 on the average latency to persistent sleep (LPS) as measured by polysomnography (PSG) on Nights 1 and 8.

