###### **14.9.2.2. Statement of the Null and Alternate Hypotheses**

Statistical analyses will be performed using two-sided test. A 0.05 significance level will be used in all tests of treatment differences. Test for interaction will utilize a 0.10 statistical significance level.

The type I error will be controlled via Fisher's protected least significant difference (LSD). Using this procedure, an overall test of the overall treatment effect will be conducted and pairwise comparisons will be examined only if the overall treatment is significant at the 0.05 alpha level. Pairwise comparisons will also be examined at the 0.05 significance level.

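### The condition for testing secondary endpoints is not tied to a dose, so a dose that misses LPS can still be claimed on secondary endpoints

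*Protocol*

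**What the plan says.** Protocol section 14.1.1 gives one primary hypothesis, on average LPS over Nights 1 and 8: "The primary null hypothesis to be tested is that there are no differences among the treatments". Fisher's protected LSD is the control for the primary endpoint. Section 14.9.2.2 repeats it: "pairwise comparisons will be examined only if the overall treatment is significant at the 0.05 alpha level". Neither section says which pairwise comparisons are meant or which of them decides the trial.

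For labeling, section 14.1.1 adds that "for labeling purposes only, the experiment wise Type I error will be controlled to a maximum of 5"%, through a gatekeeper under which "any secondary endpoints will be considered for statistical significance only if the primary endpoint to be statistically significant". No dose and no comparison with placebo is named. On levels, it says "A 0.05 significance level will be used in all tests of treatment differences" and "Pairwise comparisons will also be examined at the 0.05 significance level".

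The sizing in section 14.2 is of a different kind. It is a t-test of VEC-162 against placebo, with a 15-minute difference, SD 30, 86 per arm and 90% power.

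**The concern.** The trial is sized on a dose against placebo, while the stated primary null concerns equality of three arms and the condition for secondary testing concerns an endpoint. Two things follow if the text is applied as written.

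- **Main consequence.** Once the condition is met, it is met for both doses. If 50 mg wins on LPS and 20 mg does not, 20 mg may still be tested and claimed on WASO, TST, SE and the other secondaries. The protection that a gatekeeper should give is then missing for the dose that needs it.
- **Lesser consequence.** A difference between 20 mg and 50 mg alone can reject the stated primary null without either dose differing from placebo.

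At stake is the 5% labeling guarantee, together with the risk of a dispute, after results are known, about what counted as a primary success and for which dose.

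**Working it through.** **Inputs.** From section 14.2: difference 15 min, SD 30, 86 evaluable per arm, 1:1:1, 20% drop-out. From section 14.1.1: overall test at 0.05, then pairwise tests at 0.05, two-sided. From section 14.9.1.2: three averaged PSG secondaries on Nights 1 and 8 (WASO, TST, SE) and four on Nights 22 and 29 (LPS, WASO, TST, SE), seven in all. Assumed, because the protocol does not give them: correlation between endpoints within a patient (0 to 0.7) and the true effects in each scenario. The calculations use a one-way model without the baseline and site terms.

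**The plan's own figure.** n = 2(1.960 + 1.282)² × 30²/15² = 84.1, so 85 by the normal approximation. Exact t-test power is 89.99% at 85 and 90.3% at 86, so 86 is right. Then 86/0.80 = 107.5, rounded up to 108, and 3 × 108 = 324. The sizing reproduces, as a dose-versus-placebo calculation.

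**Dose-blind condition.** I simulated 400,000 trials per row. 50 mg improves LPS by 0.5 SD (15/30), and 20 mg is null on every endpoint. The overall F test on LPS opens secondary testing, and 20 mg is then compared with placebo on each secondary at two-sided 0.05. The table gives the chance that 20 mg has at least one significant result in its favour.

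| Secondaries | Correlation | As written | Dose-specific condition |
|---|---|---|---|
| 3 | 0 | 6.8% | 0.2% |
| 3 | 0.3 | 6.4% | 0.6% |
| 3 | 0.5 | 6.0% | 1.0% |
| 3 | 0.7 | 5.3% | 1.4% |
| 7 | 0 | 15.1% | 0.4% |
| 7 | 0.3 | 13.0% | 1.1% |
| 7 | 0.5 | 10.9% | 1.4% |
| 7 | 0.7 | 8.6% | 1.9% |

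Counting results in either direction, the as-written figures are 13.3% to 10.6% for three secondaries and 28.1% to 17.0% for seven. About half of the trials in the three-secondary count have inert 20 mg looking worse than placebo, which supports no claim.

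Reading the condition generously, as some dose beating placebo on LPS, hardly changes this: 6.5% to 5.3% for three secondaries.

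**Overall null rejected, neither dose different from placebo.** That this can happen is shown by observed differences from placebo of +5.5 min (20 mg) and −6 min (50 mg):

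- SE = 30 × √(2/86) = 4.575.
- t = 5.5/4.575 = 1.20 (p = 0.23), 6/4.575 = 1.31 (p = 0.19) and 11.5/4.575 = 2.51 (p = 0.013).
- F(2, 255) = (1.20² + 1.31² + 2.51²)/3 = 3.16, p = 0.044.

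How often it happens at 86 per arm, by true change in LPS (20 mg, 50 mg):

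| Scenario (min) | Frequency |
|---|---|
| −15, −15 | 0.002% |
| −10, −15 | 0.07% |
| −7.5, −7.5 | 0.2% |
| −7.5, −15 | 0.3% |
| 0, 0 | 0.8–0.9% |
| 0, −15 | 3.7% |
| 0, −7.5 | 6.3% |

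At 108 per arm the (0, −15) figure falls to 2.0%.

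**The case against.** **A lone 20 mg versus 50 mg difference would not be presented as efficacy.** The design is placebo-controlled, the sizing is against placebo, and no passage says that the overall test alone makes the trial positive. This stands. A reader might infer that the trial can readily succeed with neither dose working. The documents do not support that. The event needs an inert dose, or placebo lying between the doses, to be at all common, and section 4.3.2 reports that both doses shortened LPS, though in induced transient insomnia.

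**Fisher's LSD with three arms controls family-wise error for the primary pairwise tests.** Correct. The primary alpha is not inflated, and this point does not claim that it is.

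**The secondary error rate is partly a multiplicity effect.** Also correct. For a single secondary, the chance of a false favourable result for 20 mg is only about 2.4%. Exceeding 5% requires several secondaries tested without order, which is a separate matter. If LSD were also applied to each secondary, as section 14.9.2.2 could be read, and 50 mg had no effect there, the three-secondary rate would fall to about 3% in the favourable direction. Where 50 mg does move the secondaries, that protection largely disappears. Section 14.1.1 applies LSD to the primary endpoint only.

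**This is detail for the analysis plan.** Section 14.1 describes the methods only in general terms and leaves the rest to a later plan. But the protocol does not leave this open. It states an overall null, an endpoint-level condition and a 5% promise, and the three do not fit together.

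**Missing significance is not proof of no effect.** If 20 mg gives 7.5 min and 50 mg gives 15 min, 50 mg wins and 20 mg misses in about 47% of trials. That is limited power and not an error rate. It shows only how often the wording would matter.

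**Conclusion.** The concern holds for the dose-blind condition. With 50 mg effective and 20 mg inert, a false favourable secondary result for 20 mg occurs in about 5–7% of trials over three secondaries and about 8.5–15% over seven, against under 2% when the condition is dose-specific. This rests on 86 per arm, SD 30, assumed correlations of 0 to 0.7 and unadjusted tests at 0.05 on each secondary. The part arising when 20 mg failed LPS is removed entirely by a dose-specific condition. What remains is multiplicity for a dose that passes.

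The mismatch between the overall null and the dose-versus-placebo purpose is a defect of definition with small numerical effect: 0.3% or less in the scenarios where both doses work by 7.5 to 15 min, and 3.7–6.3% in those where one dose is inert. It should be corrected, but it does not mean that a primary win is generally uninformative about the drug.

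**What to change.** In sections 14.1.1 and 14.9.2.2, or in the SAP (section 14.1 allows changes of method there before database lock without an amendment):

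- Name 20 mg versus placebo and 50 mg versus placebo on average LPS (Nights 1 and 8) as the primary contrasts.
- Count the primary as met for a dose only if the overall test and that dose's comparison with placebo are both significant at 0.05 in favour of VEC-162.
- State that 20 mg versus 50 mg is descriptive and cannot make the trial positive.
- Consider a secondary endpoint for a dose only if that same dose met the primary.

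The cost is wording, with no extra patients and no change to the stated sample size. The price is that a dose that misses LPS can no longer support a secondary labeling claim. An order or adjustment among the secondaries is still needed for a dose that passes.
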